## Abstract

**Background:**

Carers of people living with dementia from culturally and linguistically diverse backgrounds experience persistent inequities in access to, and engagement with, dementia education and support services. These inequities arise from multiple service-level and systemic barriers and contribute to poorer health and wellbeing outcomes for both carers and people with dementia. Addressing these gaps remains a priority for equitable aged care. This study protocol describes an implementation science study designed to embed a culturally tailored iSupport model within routine aged care services to reduce these inequities.

**Objective:**

This study aims to implement a culturally tailored iSupport model within routine aged care services and to evaluate its effectiveness, cost-effectiveness, and implementation strategies.

**Design:**

A pragmatic, multicentre, hybrid type 1 effectiveness–implementation randomised controlled trial.

**Setting(s):**

This study will be undertaken in community aged care settings managed by seven ethno-specific aged care organisations located in three states in Australia.

**Participants:**

Carers of people with dementia from seven culturally and linguistically diverse groups will be recruited to the study (n = 150).

**Methods:**

Eligible participants will be randomly allocated to either the intervention group or the usual care control group (n = 75 per group). Participants in the intervention group will receive a culturally tailored iSupport model comprising facilitator-enabled carer psychoeducation using the iSupport for Dementia program and case studies, peer support, needs-based service navigation, and coaching delivered in carers’ preferred language and cultural context. The intervention will be delivered over 12 months. The usual care group will be directed to Dementia Australia resources and the iSupport program website only. Primary outcomes will include quality of life for carers and for people with dementia (measured via proxy reporting). Secondary outcomes will be carers’ self-efficacy, perceived social support, and reactions to changed behaviours in care recipients; changed behaviours in care recipients and their experiences of care services (proxy measures); and cost-effectiveness using a cost–utility analysis framework. Data will be collected at baseline, 6 months, and 12 months. A process evaluation will be embedded within the trial to examine implementation strategies and influencing factors, using mainly interviews with carers and focus groups with staff at 6 and 12 months.

**Registration:**

www.anzctr.org.au ACTRN12625000587404. Registered 5 June 2025. Not yet recruiting.

What is already known
•Carers of people living with dementia from culturally and linguistically diverse backgrounds experience persistent inequities in access to, and engagement with, dementia education and support services.•Embedding evidence‑based, culturally tailored education and support interventions within routine community aged care services remains challenging due to multiple barriers operating at organisational and system levels.
Alt-text: Unlabelled box dummy alt text
hat this paper adds
•This paper reports an innovative implementation science study using a hybrid type I effectiveness–implementation randomised controlled trial to evaluate the effectiveness, cost‑effectiveness, and implementation strategies of a culturally tailored iSupport model delivered within routine community aged care services.•The findings will inform community aged care organisations on how to embed the culturally tailored iSupport model into routine service delivery to address inequities in dementia education and support for carers from culturally and linguistically diverse backgrounds.•The findings will also inform policy development and funding realignment to support the scale‑up of the culturally tailored iSupport model, with the potential to reduce inequities in dementia care services and improve health and wellbeing outcomes for people living with dementia and their carers from culturally and linguistically diverse backgrounds.
Alt-text: Unlabelled box dummy alt text

## Background

1

Dementia affects >57 million people globally and is a leading cause of death and disability in countries with ageing populations (WHO, 2021). Many high‑income countries, including Australia, Canada, the United Kingdom, and the United States, have increasingly diverse populations comprising people from culturally and linguistically diverse backgrounds (United Nations, 2024). Cultural values such as filial piety, collectivism, spirituality, and religiosity strongly influence carers to provide care for family members living with dementia at home (Lillekroken et al., 2023; Yu et al., 2018). However, government‑subsidised dementia education and support programs for carers are predominantly designed for mainstream cultural groups, with limited consideration of the perspectives, needs, and preferences of carers from culturally and linguistically diverse backgrounds (Gilbert et al., 2022; Stenberg & Hjelm, 2023). The limited availability of culturally tailored interventions contributes to health inequalities among both carers and people living with dementia from those backgrounds. Health inequalities are defined as systematic, socially produced differences in health and quality‑of‑life outcomes between population groups within a society (WHO, 2024a).

People from culturally and linguistically diverse backgrounds who live with advanced dementia are more likely to remain at home rather than enter residential aged care, influenced by cultural beliefs regarding family care for older people and the limited availability of ethno‑specific nursing homes (Stenberg & Hjelm, 2023). More than two‑thirds of people with dementia also live with multiple chronic conditions, such as hypertension, diabetes, and depression, which require substantial carer involvement in ongoing management (Temedda et al., 2025). A population‑based study indicates that carers from culturally and linguistically diverse backgrounds experience disproportionately high levels of burden and social isolation. Specifically, 67% of their care recipients had profound functional limitations and an average of 5.5 chronic conditions requiring management, compared with 56% among carers from the mainstream culture (AIHW, 2022). Furthermore, 52% of people with dementia in this population spoke English poorly or not at all, resulting in heavy reliance on family carers for activities of daily living, mobility, communication, and chronic disease management (AIHW, 2025). Behavioural and psychological changes affect up to 90% of people with dementia living in the community and are a major contributor to carers’ emotional distress, burden, and reduced quality of life (Feast et al., 2016). Despite these substantial care demands, accessible and culturally and linguistically tailored emotional support and behavioural management programs for carers remain very limited (AIHW, 2025).

Lack of preparedness for the caregiving role has been linked to low carer self‑efficacy, increased care complications, and avoidable hospital admissions (Bott et al., 2019). Language barriers limit carers in participating in publicly funded dementia education and support programs (Lillekroken et al., 2023; Yu et al., 2024). Evidence from a population‑based study in the United States suggests that approximately 40% of dementia‑related hospitalisations may be preventable through adequate carer education and support (Anderson et al., 2020). Carers from culturally and linguistically diverse communities often experience erosion of pre‑migration social support networks, leading to social isolation and limited access to peer support opportunities (Lai et al., 2019; Yu et al., 2024). Adult children caring for parents with dementia are particularly common in culturally and linguistically diverse communities, and this group is more likely to be engaged in paid employment, increasing their vulnerability to role strain (Lillekroken et al., 2023).

### The culturally tailored iSupport model to mitigate dementia care challenges

1.1

It is estimated that >28% of people living with dementia in Australia (>115,108) are from culturally and linguistically diverse backgrounds, and 79% of this population live at home and are supported by family carers (AIHW, 2025; DoHA, 2024). Carers from culturally and linguistically diverse backgrounds account for approximately 32% of the national dementia carer population (>107,904) and experience a disproportionately high dementia care burden (AIHW, 2025; DoHA, 2024). Despite this substantial need, dementia education and support programs tailored for culturally and linguistically diverse carers remain very limited (AIHW, 2025).

The culturally tailored iSupport model that will be evaluated in this study comprises three intervention components as outlined in Fig. 1. It will be delivered to carers in their preferred language and culture by trained facilitators. The three components in the model has previously been tested in a randomised controlled trial involving carers from the mainstream population in Australia (Xiao et al., 2025a). The trial showed that the iSupport model can improve carers’ health and wellbeing and reduce hospital admissions among people living with dementia. This body of evidence, together with strong national and international policy imperatives to promote health equity for people living with dementia and their carers (DoHA, 2024; WHO, 2017), provides a compelling rationale for applying an implementation science study to accelerate the translation of evidence into routine community aged care services.

**Fig. 1 fig0001:**
[figure not shown]
The culturally tailored iSupport model for culturally and linguistically diverse carers.

#### Culturally tailored psychoeducation program for carers

1.1.1

The psychoeducation component of the model is the iSupport for Dementia program, originally developed by the World Health Organization (WHO, 2019, 2021) and culturally adapted in Australia in eight languages: English, Greek, Bahasa Indonesia, Italian, Simplified Chinese, Spanish, Traditional Chinese, and Vietnamese. The program comprises six modules and 30 units. The modules include: Introduction to dementia; Being a carer; Caring for yourself; Providing everyday care; Dealing with changed behaviour; and My engagement in consumer‑directed care (see Supplementary File 1).

The iSupport program incorporates principles of person‑centred care, problem‑solving strategies, and self‑care through evidence‑informed case studies, enabling carers to build dementia‑specific knowledge, practical caregiving skills, and positive caregiving appraisals. These elements support carers to manage daily care tasks, prevent or respond to changed behaviours, and improve care outcomes for people living with dementia, while reducing carers’ stress and burden (Pot et al., 2019). Where appropriate, the program also introduces carers to relevant dementia care resources and multidisciplinary services to facilitate access and utilisation. Carers are encouraged to select units most relevant to their individual learning needs and incorporate them into a personalised study plan.

Consultations with key stakeholders prior to this study identified a lack of culturally tailored case studies to support carers in managing changed behaviours, chronic conditions (e.g. diabetes and hypertension), late‑stage dementia, and palliative care within an Australian sociocultural context (Xiao et al., 2026a). Stakeholders also expressed a strong preference for short videos that simulate real‑world care scenarios and could be used for self‑coaching or facilitator‑led coaching to support achievement of carers’ learning goals (Xiao et al., 2026a). To address the identified limitations, a book entitled “Culturally tailored case studies for dementia carers” with videos and podcasts was co‑designed and co-produced with stakeholders to align with the 6-module iSupport program. The case studies address: (1) caring for a person with memory loss; (2) supporting carers at the time of dementia diagnosis and beyond; (3) enabling culturally tailored self‑care for carers; (4) supporting carers in late‑stage dementia care; (5) enabling carers to support loved ones experiencing changed behaviours; and (6) enabling carers to access appropriate care services. Collectively, these comprise 56 short case scenarios presented through 54 videos and 2 podcasts (see Supplementary File 1).

#### Carer peer support

1.1.2

Preparing staff from aged care organisations to act as facilitators of carer support groups is an effective strategy to reduce social isolation and promote peer support among carers (Xiao et al., 2026b; Yu et al., 2024). Online peer support enables carers to reinforce positive caregiving appraisals, observe role modelling, enhance self‑efficacy, and reduce caregiving‑related stress (Etxeberria et al., 2021). Findings from our feasibility study demonstrated that facilitator‑led, monthly online peer support meetings of one hour’s duration, combined with weekly text‑based interactions via social media platforms such as WhatsApp or WeChat in small groups (5–10 carers per group), were acceptable to carers (Xiao et al., 2025b).

#### Needs-based care service navigation and coaching support

1.1.3

Trained personnel–led care service navigation for carers can address barriers within health and aged care systems, facilitate timely access to services for care recipients, prevent care crises, and reduce avoidable hospital admissions and emergency department utilisation (Kallmyer et al., 2023). Carers from culturally and linguistically diverse backgrounds have expressed a strong preference for facilitators who share their cultural and language background to support navigation of care services and overcome language barriers (Xiao et al., 2026a; Yu et al., 2024).

Carers also desire to contact facilitators for coaching support to develop problem‑solving skills when managing chronic conditions, complications, and changed behaviours affecting their care recipients (Xiao et al., 2026a). Guided by a health coaching framework (Wolever et al., 2013), coaching within the psychoeducation component of this study is defined as facilitator‑enabled processes that include learning needs assessment, goal setting, and active engagement in dementia care education through the iSupport program and the “Culturally tailored case studies” and/or related videos. To operationalise this approach, we co-developed a coaching tool for carers (Supplementary File 2) and a coaching tool for facilitators (Supplementary File 3) prior to this study.

## The study

2

### Aims

2.1

The aims of this study are to implement a culturally tailored iSupport model within routine aged care services and to evaluate its effectiveness, cost-effectiveness, and implementation strategies.

### Hypotheses

2.2

#### Primary hypotheses

2.2.1

Compared to carers allocated to the usual care group, 1) carers receiving the culturally tailored iSupport model will report (a) at least a 5-point higher mean score on the mental component of the 12-Item Short-Form Health Survey and (b) an improved mean score on the physical component of the survey; 2) their care recipients will report an improved mean score on the Quality of Life in Alzheimer’s Disease-Proxy at 12-month follow-up.

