#### Study setting, participants and sample size

2.4.2

This study will be undertaken in community aged care settings managed by seven ethno‑specific aged care organisations located in three states in Australia. The estimated minimal sample size for carers in the study is 100 with 50 carers in the intervention group and 50 in the usual care group. This sample size is based on a primary outcome of the mental component of the 12-Item Short-Form Health Survey and an assumption of a 0.57 effect size reported in a previous trial using a multicomponent intervention for carers of people with dementia (Berwig et al., 2017), with an 80% power to detect a difference between means of 4.93 with a pooled standard deviation of 8.63 in the study. However, considering a 50% attrition rate in a 12-month trial in our previous project, we will need to recruit 150 carers to the trial or 75 carers in the tailored iSupport group and the usual iSupport group respectively.

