##### Intervention effectiveness

2.4.7.1

Data analysis will be led by a statistician who will be blinded to group allocation. All analyses will be conducted according to the intention‑to‑treat principle, with participants analysed in their assigned groups. Multivariable linear mixed‑effects models will be used to examine differences in primary and secondary outcomes between groups over time. Given the repeated measurements for each participant, mixed‑effects models will account for both fixed and random effects within the hierarchical data structure. Fixed effects will include group, time, and group‑by‑time interaction terms, while random effects will model individual‑level variability in intercepts to account for within‑participant correlation. Models will be adjusted for baseline values of the outcome variables. Maximum likelihood estimation will be used to assess between‑group differences and changes over time.

Univariate mixed‑effects models will be fitted initially, followed by multivariate models incorporating variables identified as clinically relevant or statistically significant in univariate analyses to control for potential confounding. Model building will involve sequential addition and removal of covariates, with changes in model fit evaluated using log‑likelihood statistics to determine the final multivariate model. All statistical tests will be two‑sided, with statistical significance set at p < 0.05. Analyses will be performed using Stata version 16.1 and R version 4.2.2.

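### Three primary scores are each tested at two-sided 0.05 with no testing order or success rule, and only one of them was used to size the trial

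*Protocol article*

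**What the plan says.** The abstract (Methods) does not rank the primary outcomes: "Primary outcomes will include quality of life for carers and for people with dementia". Section 2.2.1 turns this into three hypotheses at 12 months. The first asks for "at least a 5-point higher mean score on the mental component of the 12-Item Short-Form Health Survey". The second and third follow directly: "b) an improved mean score on the physical component of the survey; 2) their care recipients will report an improved mean score" on the proxy QoL-AD. Section 2.4.5.2.1 lists the same instruments as primary and confirms that the SF-12 yields two summary scores, so there are three primary scores in all.

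Section 2.4.7.1 makes all tests two-sided, with "statistical significance set at" p < 0.05. Section 2.4.2 says: "This sample size is based on a primary outcome of the mental component". It gives 80% power for that score and no power for the other two. No section says how the three results combine into a verdict on the trial.

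**The concern.** With three primary scores and one per-test threshold, the meaning of a positive trial is left to the reader. A reader who accepts any one significant score could count success on the physical score or the proxy score, neither of which was used for sizing, when the mental component shows nothing. A reader who requires all three would find that the sample-size section does not say how likely that is. The article expects its findings to inform policy and funding, and section 3.4 accepts that carers know their allocation. The choice of deciding outcome should therefore be made before the results are seen.

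**Working it through.** **Inputs.** Three primary scores (2.2.1, 2.4.5.2.1); two-sided 0.05 per test (2.4.7.1); difference 4.93, SD 8.63, power 80%, 50 per group (2.4.2). The document gives no correlations between the scores, so those below are assumed.

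**1. The plan's own sample size.** Effect size d = 4.93 / 8.63 = 0.571. Per group, n = 2(1.960 + 0.842)² / 0.571² = 48.1, which rounds up to 49 (normal approximation). The t-test version gives 49.1, rounded up to 50. The stated 50 per group is reproduced. It matches one two-sided test at the full 0.05 on the mental component, with nothing set aside for the other two scores. Power at 50 per group is 80.7% by t-test.

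**2. If any one significant score counts as success.** With all three null hypotheses true and the scores independent, P(at least one p < 0.05) = 1 − 0.95³ = 14.3%. Simulation of three equally correlated normal statistics (1,000,000 draws per value) gives:

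| Assumed pairwise correlation | At least one false positive, either direction |
|---|---|
| 0 | 14.3% |
| 0.3 | 13.6% |
| 0.5 | 12.5% |
| 0.7 | 10.9% |
| 0.9 | 8.4% |

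The hypotheses are directional, so the false claim of most interest is one of benefit. Each two-sided test has a 2.5% chance of that under the null. For three independent scores, 1 − 0.975³ = 7.3%, against 2.5% for a single test. By the same simulation it is 6.3% at correlation 0.5 and 4.2% at 0.9.

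**3. If all three scores must succeed.** The error rate is not inflated. Joint power cannot exceed the power of the weakest score, so it is at most 80.7% at 50 per group. It may be much lower, because no effect size or power is given for the other two scores.

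**4. Cost of the remedies.** A Bonferroni split tests each score at 0.05 / 3 = 0.0167. At 50 per group, mental-component power falls from 80.7% to 66.3% (t-test). Restoring 80% needs 65 per group by the normal approximation, or 66 by t-test. A fixed sequence that starts with the mental component keeps it at 0.05, so its power and the sample size do not change, and the family-wise error for the three scores stays at 5%.

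The power figures assume 50 completers per group and an unadjusted comparison. The planned model adjusts for baseline, so they serve to compare remedies and do not forecast the trial's power.

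**The case against.** The strongest reply is that the threshold in section 2.4.7.1 is a generic per-test level. It does not exclude a testing order, and a fixed sequence would also use 0.05 at each step. An order could be in a full protocol or analysis plan that is not shown. The mental component also looks like the lead outcome: it is listed first, is the only score with a numerical target, and is the sizing outcome.

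Part of this stands. The article does not contradict itself, and the remedy fits its stated threshold. However, which outcome is primary and what counts as success are protocol matters, and the article does address them: it gives three scores equal primary standing at one threshold. The lead role of the mental component can only be inferred, since section 2.4.2 calls it a primary outcome, not the primary outcome.

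A reader might infer three stronger points, which the document does not support:

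- **That the trial has a 14% false-positive rate.** That figure needs four conditions together: any one score suffices, all three null hypotheses are true, the scores are independent, and results in either direction count. The same carer reports all three scores, so positive correlation is plausible and would lower it.
- **That the stated 5% is false.** Section 2.4.7.1 gives a per-test level and never claims a family-wise one.
- **That the stated 80% power is false.** Section 2.4.2 attaches it expressly to the mental component.

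**Conclusion.** The point holds as a gap in the decision rule: there are three primary scores, one unadjusted threshold, no order or success rule, and sizing on one score. If any one score suffices and all three null hypotheses are true, the chance of a false-positive primary result is 14.3% at independence and 8.4% at an assumed correlation of 0.9. For benefit only, it is about 7.3% at independence, against 2.5% for one test. If all three must succeed, the error rate is sound, but the joint power is unstated. The document does not say which reading applies, so neither consequence can be assigned to the trial as a fact. This should be fixed. It is a cheap improvement to the plan and does not show that a stated figure is wrong.

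**What to change.** Before recruitment (the registration entry in the abstract says it has not begun), state that the 12-month between-group difference in the SF-12 mental component decides trial success, tested at two-sided 0.05. Test the other two primary scores in a pre-specified fixed sequence at 0.05, each only if the preceding test is significant, or call both key secondary. The sponsor should choose the order; the one listed in section 2.2.1 (physical component, then proxy QoL-AD) would do, and nothing in the document calls for reversing it. If the sponsor prefers to require all three, say so and give the joint power.

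The cost is wording in the hypotheses, the analysis section and the registry entry. The downside is that a later outcome gets no confirmatory claim if an earlier one fails. Sample size and mental-component power are unchanged under the fixed sequence.
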